##### *Concomitant medications authorized with anti-TNFα, anti-Il-6R, and CTLA-4*

These include any conventional synthetic DMARD that the patient was previously taking before being included in the study and that his rheumatologist deems necessary to continue. Oral corticosteroids at dose ≤15 mg/day, intravenous corticosteroids, intraarticular, and peri-articular local injections of corticosteroids, salicylates, nonsteroidal anti-inflammatory drugs (NSAIDs), analgesics, drugs necessary for the treatment of comorbidities, concomitant treatment with corticosteroids, NSAIDs, and analgesics showed no effect on the pharmacokinetics of these biotherapies.

##### Criteria for discontinuing or modifying allocated interventions {11b}

The discontinuing or modifying allocated interventions for a given trial participant in the study will be as follows: lack of response to medication in the intermediate visit (3 months after inclusion) using the EULAR response criteria; occurrence of adverse events, including malignancy; loss to patient follow-up; withdrawal of consent by the patient; decision of the investigator (inadequate follow-up of the instructions of the doctor or study staff); the rheumatologist or the promoter (medical monitor) decides that continuing the study can be harmful to the patient; in case of pregnancy (only if the patient is under treatment with a therapy that does not recommend pregnancy; in the event that the medication is compatible with the pregnancy, the patient can still be included in the study); in case the patient needs a treatment or has received some treatment not allowed in the study; erroneous inclusion in the study; circumstances not foreseen; cancelation of the study.

Patients discontinuing the intervention will not be followed up and will be withdrawn from the study.

No treatment / procedure prohibited during the study.

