The bDMARDs possibly recommended by SinnoTest® are adalimumab, rituximab, and abatacept. Not being exhaustive in terms of biotherapies, it is possible that the SinnoTest® cannot recommend any bDMARD. In this case, the rheumatologist may prescribe one of the following other bDMARDs: etanercept, adalimumab, infliximab, certolizumab, tocilizumab, sarilumab, abatacept, anakinra, golimumab, or rituximab.

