##### Relevant concomitant care permitted or prohibited during the trial {11d}

No restrictions regarding concomitant care were enacted during the trial. The only limitations were those imposed by usual care: concomitant synthetic DMARDs were allowed, corticosteroid dosage could be modified as required, intraarticular corticosteroid injections were allowed.

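### Use of or need for a non-allowed treatment can end follow-up before month 6, although the text says no treatment is prohibited and the analysis is by intention to treat

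*Protocol article*

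**What the plan says.** Four parts of the protocol article bear on this.

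- **Criteria for discontinuing or modifying allocated interventions {11b}.** One listed ground is "in case the patient needs a treatment or has received some treatment not allowed in the study". After the list: "Patients discontinuing the intervention will not be followed up and will be withdrawn from the study". The section ends: "No treatment / procedure prohibited during the study".
- **Relevant concomitant care {11d}.** "No restrictions regarding concomitant care were enacted during the trial". It adds that the only limits are those of usual care, and illustrates them with permissions: "concomitant synthetic DMARDs were allowed, corticosteroid dosage could be modified as required".
- **Concomitant medications authorized.** This list names "any conventional synthetic DMARD that the patient was previously taking before being included in the study" and "Oral corticosteroids at dose ≤15 mg/day, intravenous corticosteroids, intraarticular, and peri-articular local injections of corticosteroids".
- **Biologics.** Under Innovative procedure, if the software recommends nothing, the rheumatologist may choose from "etanercept, adalimumab, infliximab, certolizumab, tocilizumab, sarilumab, abatacept, anakinra, golimumab, or rituximab". The list for usual care under Reference procedure is the same without sarilumab, while section {11a} gives the control arm every bDMARD.

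On the analysis side, the clinical primary outcome is EULAR response at 6 months. Section {20c} specifies intention to treat whatever intervention is received, multiple imputation with sensitivity analyses, and an additional per-protocol analysis. It also keeps disallowed medication as a coded reason for leaving. Section {18b} wants participants taught that research follow-up matters even after study drug is stopped. Section {14} adds nothing for loss to follow-up.

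**The concern.** Section {11b} makes disallowed treatment a possible route out of the study and, in its closing line, says there is no such treatment. A site has to decide for itself whether, say, a patient raised above 15 mg/day of oral corticosteroid is withdrawn or kept.

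The loss does not depend on how that is settled. The trial compares two ways of choosing a biologic, analysed as randomized. A change of concomitant or antirheumatic treatment is no reason to stop measuring the outcome in such a comparison. A patient withdrawn on this ground before month 6 has no observed primary outcome, although the visit is already scheduled and the patient may be willing to attend. The value must then be imputed. The reason for leaving may also be related to disease activity, since steroid escalation often is, so an observed DAS28-ESR is worth more than an imputed one.

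**Working it through.** **1. The texts side by side**

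| Question | Reading that removes the patient | Reading that keeps the patient |
|---|---|---|
| Is any treatment disallowed? | {11b} list: yes, and it is a ground for discontinuing or modifying | {11b} closing line: none prohibited |
| Oral steroid above 15 mg/day | Authorized list stops at 15 mg/day | {11d}: dose modified as required |
| Follow-up after discontinuing | {11b}: none, withdrawn | {18b}: follow-up still important; {20c}: analysed as randomized |

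Possible content for the disallowed category includes the 15 mg/day figure, a biologic outside the two lists, or a treatment received in another therapeutic trial, which {10} makes an exclusion. Under each of these, stopping follow-up has the same result: no month-6 response for a patient the primary analysis must include.

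**2. The plan's own sample size**

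Inputs from {14}: control response p1 = 0.65; difference 0.182, so p2 = 0.832; two-sided alpha 5%; 90 per arm; 80% power.

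Pooled-variance formula without continuity correction, with p̄ = (0.65 + 0.832)/2 = 0.741:

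power = Φ{ [ (p2 − p1)√n − 1.96·√(2p̄(1 − p̄)) ] / √(p1(1 − p1) + p2(1 − p2)) }

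- √(2 × 0.741 × 0.259) = 0.6195, times 1.96 = 1.2143
- √(0.65 × 0.35 + 0.832 × 0.168) = √0.3673 = 0.6060
- n = 90: 0.182 × √90 = 1.7266; (1.7266 − 1.2143)/0.6060 = 0.845; Φ(0.845) = 0.801

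The stated 90 per arm for 80% power is reproduced.

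**3. Effect of losing patients on this ground**

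The article gives no frequency. The rates below are assumptions, and lost patients are taken to contribute no information.

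| Lost per arm (assumed) | Patients of 180 | Effective n per arm | 0.182√n | Power | Loss from 80.1% |
|---|---|---|---|---|---|
| 1% | 1.8 | 89.1 | 1.7179 | 79.7% | 0.4 points |
| 2% | 3.6 | 88.2 | 1.7093 | 79.3% | 0.8 points |
| 5% | 9 | 85.5 | 1.6829 | 78.0% | 2.1 points |

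These are pessimistic for the given rates. Table 1 schedules assessments at M0 and M3, and multiple imputation can use them to recover part of the information.

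**The case against.** The strongest case on the other side has five parts.

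- **The category is not empty.** A reader might infer that disallowed treatment can only mean the authorized-medication list or the biologic lists, so that the ground has no meaning elsewhere. The article does not support that: {10} bars patients in another therapeutic trial, and {11d} keeps the limits of usual care. A reader might likewise take {11d} to leave concomitant care wholly unrestricted; its next sentence says otherwise. This part stands.
- **The two concomitant-care texts conflict less than they seem to.** Allowing synthetic DMARDs in {11d} does not say that new ones may be added, so it is compatible with the authorized list. Only the steroid item is in tension, and the list attaches no withdrawal to the 15 mg/day figure. This stands.
- **Withdrawal is not automatic.** {11b} covers discontinuing or modifying, and the no-follow-up sentence applies only to those who discontinue. This also stands and limits how many patients can be affected. It does not help the patient who does discontinue.
- **This is a condensed article.** A list of disallowed drugs may sit in the full protocol, so the missing definition is not itself a fault. The contradiction inside {11b} and the no-follow-up rule are, however, stated in the text, and a list would not cure the second.
- **The effect is small, and imputation is planned.** True. But imputation deals with values already missing; it does not justify creating them.

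The same no-follow-up sentence also applies to the other grounds in {11b}, such as lack of response at 3 months. Those are outside this point.

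**Conclusion.** The point holds in a limited form. As written, {11b} can end follow-up because of a treatment change and so lose an obtainable month-6 EULAR response. That is inconsistent with its own closing line, with the retention aim in {18b} and with the intention-to-treat analysis in {20c}. The conclusion does not depend on what the disallowed category contains.

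The size is probably small: 0.4 to 2.1 points of power at assumed losses of 1% to 5% per arm contributing nothing, and less with imputation. The true number is unknown.

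Two stronger conclusions are not supported. A reader might infer a bias towards one arm, but nothing in the article gives a direction, and {17a} blinds patients and evaluators. A reader might also infer that the 15 mg/day limit has to go. It does not: the limit can stay as a treatment rule, provided exceeding it does not end follow-up. The change is worth making because it is cheap and protects the primary outcome, not because the expected loss is large.

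**What to change.** Amend {11b} so that use of or need for a non-allowed treatment may change or stop the biologic but does not end follow-up. Unless consent is withdrawn, the patient:

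- attends month 6 for DAS28-ESR;
- is analysed in the randomized arm;
- has the drug, dose and dates recorded in the concomitant-treatment collection already in Table 1.

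Use the deviation only for the per-protocol analysis that {20c} already plans, and keep the disallowed-medication code there as a description of the deviation. Reconcile the closing line of {11b} and the steroid wording of {11d} with the 15 mg/day figure. The stop on grounds of harm to the patient is unaffected.

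Trial status says that recruitment has restarted, so the amendment should be issued now, with a list by arm and site of anyone already withdrawn on this ground.

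The cost is one short amendment, with no new visits or data items. The downside is that some month-6 responses will partly reflect an added drug. That suits a comparison of prescribing strategies, and the per-protocol analysis examines it.

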The prices of drugs dispensable through pharmacies will be obtained from the Database of the Spanish Official College of PharmacistsThe prices of hospital dispensing drugs will be obtained from the Pharmacy Services of each participating center.The costs of the different medical acts (first visits or revisions, in primary or specialized care, by different medical professionals) will be provided by each participating center.The costs of hospitalizations and the procedures that are carried out will be provided by each participating center.The costs of the complementary tests will be obtained from each participating center.The use of home assistance will be evaluated based on a standard average cost. The cost of employing professionals from the medico-social sector (for example, occupational therapist) will be estimated based on an average cost per hour.The cost of improvements in the home will be estimated, as far as possible, in the billing data or in the data obtained by the professionals of the sector involved.In relation to the costs of caregivers (non-professionals) and the loss of production of the patient, according to the recommendations, the direct costs will take into account the time of the people intervened and the time that the caregivers dedicate to the care of the patients. However, in relation to the valuation method, there is no agreement on the method to be used. We will favor the human capital method, where the “value” of an individual is estimated by its productive value in the labor market, that is, through the gross salary. These productive costs will be obtained through the data of age, sex, and professional sector of the individual through the national statistics available on the Spanish Social Security website.The cost of medical transport will be assessed through the rates established based on the distance and type of vehicle.

We consider that 6 months is enough time to assess the performance of the intervention. According to the EULAR recommendations for biotherapy management in rheumatoid arthritis [25], 6 months is the time to assess if the therapeutic objectives of the medication has been achieved (remission or at least low disease activity). Based on those recommendations, if the patient is still active, treatment should be modified.

Incremental cost-effectiveness ratio at 6 months (time frame: 6 months)

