### Sample size {14}

To re-evaluate the metrological properties of SinnoTest®, including 90 patients per group will highlight a differential response rate between the software arm and the control arm of more than 18.2%, considering a current response rate of 65% (defined as an EULAR good response [24]) with conventional care (control arm). The number of subjects required was estimated considering a bilateral alpha risk at 5% and a power of 80%. In total, 180 patients will be the estimated number of participants needed to achieve study objectives.

Due to the subject’s and the study’s characteristics, no allowance for loss to follow-up was considered in the sample size calculation: patients with a chronic disease, probably being followed up in the same center and by the same rheumatologist for some time (> 1 year), and the short follow-up time for the primary outcome.

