#### Plans to promote participant retention and complete follow-up {18b}

In order to maximize the retention rate of the subjects included in the study, several strategies will be put in place:
Participants will be asked to provide both phone and email addresses, as well as the best time to contact them.Study subjects will also be educated in the significance of research follow-up even if they decide to discontinue the study drugs. Explaining how their experiences with the treatments, whether positive or negative, are critical to evaluating the intervention under study can increase their understanding of the research process and lay the groundwork for future discussions about the importance of completing research assessments.Anticipated barriers to attending appointments such as transportation, work schedules, vacations, and childcare can be reviewed up front and resolved.Phone calls regarding study visit reminders will be used for all appointments, and rapid follow-up of missed appointments will be incorporated into the protocol.The schedule of study visits will be flexible, ensuring subject retention.

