### Methods in analysis to handle protocol non-adherence and any statistical methods to handle missing data {20c}

Analyses will be carried out by intention to treat (i.e., each patient will be considered to belong to the group to which they were randomized, regardless of the intervention they receive).

For each patient that leaves the study before its completion, the cause will be collected, which will be classified as follows: lack of response to biotherapy, occurrence of adverse events, loss to follow-up, withdrawal of consent, the investigator’s decision, use or need for medication not allowed, erroneous inclusion in the study, unforeseen circumstances, or cancelation of the study.

To handle missing data, multiple imputation techniques will be applied [31], in addition to sensitivity analysis with the object to check the assumptions made in the imputation, and check whether the conclusions of the study are modified, or not, according to the analysis strategy adopted. The multiple imputed dataset will be used to perform the primary and secondary outcome analyses.

In addition, we also will carry out a per-protocol analysis of the primary and secondary outcomes.

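### Withdrawing and not following patients who discontinue, including for non-response at month 3, leaves the as-randomized month 6 response, QALYs and later costs unidentified

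*Protocol article*

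**What the plan says.** - **Discontinuation, {11b}.** The listed reasons begin with "lack of response to medication in the intermediate visit (3 months after inclusion) using the EULAR response criteria". The section then says: "Patients discontinuing the intervention will not be followed up and will be withdrawn from the study". Its title and list cover both discontinuing and modifying the allocated intervention; the no-follow-up sentence names only discontinuing.
- **Missing data, {20c}.** Lack of response to biotherapy is the first listed cause of leaving the study. Patients are analysed in the arm to which they were randomized, whatever treatment they go on to get. "To handle missing data, multiple imputation techniques will be applied", for primary and secondary outcomes, with sensitivity analyses of the imputation assumptions and a per-protocol analysis.
- **Follow-up, {8} and {18b}.** Every patient is to be followed to 6 months clinically and to 12 months for budget impact. On retention: "Study subjects will also be educated in the significance of research follow-up even if they decide to discontinue the study drugs".
- **Outcomes, {12} and {20a}.** The primary outcome is EULAR response at M6 on DAS28-ESR, compared by adjusted logistic regression. QALYs use EQ-5D at M0, M3 and M6. The cost-effectiveness ratio divides by the difference in response rates.
- **Sample size, {14}.** 90 per arm, with no allowance for loss to follow-up.

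**The concern.** The reason for withdrawal is the primary outcome measure read three months early. A patient who fails at M3 leaves before the outcome can be observed, so the data are missing because of failure. If the arms differ in failures, as the trial hopes, they will probably differ in missingness too.

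This is a data-collection rule, not an analysis detail: no analysis plan can recover an M6 DAS28, an M6 EQ-5D or M6 to M12 costs that were never collected. The economic outcomes are the most exposed. The Background {6a} cites a study in which patients who changed bDMARD cost the health system more than those who did not. Those are the costs the software is meant to reduce, and they would go uncounted.

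**Working it through.** **1. The plan's own figure.** Inputs from {14}: control rate 65%, detectable difference 18.2 points (so 83.2% with the software), two-sided alpha 5%, power 80%. Pooled-variance formula, with mean rate 0.741:

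n = [1.96·√(2·0.741·0.259) + 0.8416·√(0.65·0.35 + 0.832·0.168)]² / 0.182² = [1.2143 + 0.5100]² / 0.0331 ≈ 89.8, so 90 per arm. Power at 90 is 80.1%. The stated size is reproduced.

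**2. Illustration: complete-case analysis, or imputation that ignores M3 status.** The documents give no M3 non-response rate. Assume that a share f of M6 non-responders is withdrawn at M3, and that everyone withdrawn would have been an M6 non-responder. For an arm with true rate p:

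- share missing = (1−p)·f
- rate among observed = p / [1 − (1−p)·f]
- patients observed = 90·[1 − (1−p)·f]

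| f, both arms | Missing, control / SinnoTest | Observed rates | Difference | Power |
|---|---|---|---|---|
| 0 | 0 / 0 | 65.0% / 83.2% | 18.2 | 80% |
| 25% | 8.8% / 4.2% | 71.2% / 86.8% | 15.6 | 71% |
| 50% | 17.5% / 8.4% | 78.8% / 90.8% | 12.0 | 56% |
| 75% | 26.3% / 12.6% | 88.1% / 95.2% | 7.1 | 35% |

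For f = 50%: 0.65/0.825 = 0.788 and 0.832/0.916 = 0.908. Power is from the pooled two-proportion test on the reduced numbers.

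**3. Odds ratio.** The odds among observed patients are p / [(1−p)(1−f)], so the observed odds ratio is the true one times (1−f_control)/(1−f_SinnoTest). The true value is (0.832/0.168)/(0.65/0.35) = 2.67.

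- Equal f: stays at 2.67.
- f = 50% control, 25% SinnoTest: 2.67·0.50/0.75 = 1.78; difference 86.8 − 78.8 ≈ 8 points.
- f = 25% control, 50% SinnoTest: 2.67·0.75/0.50 = 4.0; difference 90.8 − 71.2 = 19.6 points.

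Both measures can therefore move in either direction.

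**4. What multiple imputation can and cannot do.** DAS28 was simulated at M0, M3 and M6 for 90 per arm, calibrated to 65% and 83.2% at M6 (600 replicates, 20 imputations, linear model within arm). Assumed inputs include a baseline mean of 5.2 (SD 0.9) and an M3–M6 residual correlation of 0.6. Differences are in percentage points.

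| Who is withdrawn at M3 | Missing, control / SinnoTest | Imputed without M3 DAS28 | Imputed with M3 DAS28 | Had all stayed on drug | As-randomized: no switched patient responds | As-randomized: half respond |
|---|---|---|---|---|---|---|
| EULAR non-responders | 12% / 5% | about 15 | about 18 | about 18 | 19.3 | 15.8 |
| All short of a good response | 52% / 34% | about 9 | about 18 to 18.5 | about 18 | 20.5 | 11.6 |

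With M3 DAS28 in the model, imputation recovers the effect had patients stayed on their drug. It returns that same answer whatever happens after a switch, because no post-switch outcome is ever observed. The effect defined in {20c}, as randomized whatever treatment follows, is not identified.

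**The case against.** The strongest reply is that the planned analysis is not complete-case. Disease activity, EQ-5D and HAQ are measured at M3, so the variable driving withdrawal is observed beforehand, and a sensible imputation model would include it. The primary comparison is an odds ratio, which is unchanged when f is equal in both arms. {20c} already plans sensitivity analyses and records the cause of leaving. All of this stands, and it rules out reading the 12.0 points and 56% power as a forecast of this trial. It does not restore the as-randomized effect, nor does it protect the rate difference, QALYs or costs.

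Two more points stand. The assumed f links lack of response at M3 to failure to reach a good response at M6, and the article does not say that these groups coincide. Also, the no-follow-up sentence names discontinuing only, so it is one reading, not a certainty, that every M3 non-responder loses the M6 outcome.

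A reader might also see a contradiction with the outcomes section, where "6 months is the time to assess if the therapeutic objectives of the medication has been achieved". That conflict is weak: an early check for failure at M3 and a treatment target judged at M6 can coexist.

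**Conclusion.** The point holds as a fault in the follow-up rule. As written, {11b} ends data collection on patients who discontinue for early failure, against {8}, {18b} and the intention-to-treat definition in {20c}, and the zero allowance in {14} ignores a loss that the protocol itself creates. The as-randomized response difference, the M3–M6 part of the QALY and the costs after a switch are then not identified. The cost-effectiveness and cost-utility ratios, and the budget impact if it is carried out, are at risk of bias.

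A reader might infer that the imputed analysis is certainly biased, that both response rates are inflated, or that intention to treat cannot be delivered at all. The documents do not support this. The M3 non-response rate, the imputation model and response after a switch are not given, so neither size nor direction can be fixed. The 7.1 to 15.6 points and 35% to 71% power rest on the assumed f and on an analysis that ignores M3 status.

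**What to change.** Replace the no-follow-up sentence in {11b}: patients who stop or change the assigned bDMARD stay in the study and complete the assessments already scheduled, unless they withdraw consent. In Table 1 these are DAS28, EQ-5D, HAQ and the patient booklet at M6, and the booklet alone at M12.

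Use these data in the intention-to-treat, QALY, cost and budget-impact analyses. Limit multiple imputation to patients truly lost, with M3 measures in the model. As a sensitivity analysis, count missing outcomes and discontinuation for lack of response as non-response. Making that the primary rule would be a choice of estimand, since a patient who switches and responds by M6 would count as a failure; it would have to be stated as such.

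Reconcile {8}, {11b}, {18b} and {20c}, including whether modifying treatment also ends follow-up. This concerns follow-up and analysis only; no clinical switching rule is proposed.

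The cost is a protocol amendment and some extra follow-up effort, with no new visit. Recruitment began in December 2019, so data on any patients already withdrawn may not be recoverable. With everyone followed, the design keeps 90 per arm and 80.1% power if the as-randomized rates are 65% and 83.2%. If patients respond after a switch, the true difference itself is smaller: with f = 50% and half of those withdrawn responding, 65 + 35·0.5·0.5 ≈ 73.8% and 83.2 + 16.8·0.5·0.5 = 87.4%, a difference of 13.6 points with 64% power.

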### Participant timeline {13}

This study will be conducted by rheumatologists who have the opportunity to follow patients with RA and to conduct this study in good conditions and in accordance with regulatory and legal recommendations. The only difference in follow-up between the 2 groups is the addition of the “SinnoTest® Protein Biomarker” assay and the use of the results of this assay for therapeutic management.

Patients will be seen as part of their follow-up consultation in the Rheumatology department:
-Screening: verification of the eligibility criteria.-Inclusion or M0 visit: after information and signature of informed consent. All patients will have a SinnoTest® blood sample. At the end of this visit, the patient is randomized to the SinnoTest® group or the control group. In the control group, the SinnoTest® sample is kept but not analyzed.-6–10 days after the consultation, the prescription of the biotherapy recommended by the rheumatologist is sent by post. This prescription uses SinnoTest® results in the SinnoTest® arm.-Followed quarterly: M3 and M6.

As part of the proteomics substudy, for those patients who agree to participate, blood samples will be collected from the 2 groups in the M0 and in the M6 to study the variations in the proteomic profile of the patients. In addition, the remaining samples will be deposited in a biobank (in the recruitment center and in the Biobank of the Center Hospitalier Universitaire Grenoble Alpes, France). The participant timeline is presented in Table 1.

**Table 1 Tab1:** Schedule of enrollment, interventions, and assessments

Visits	Selection	Inclusion^a^ M0	M3 ± 2 weeks	M6 ± 2 weeks	M12 ± 2 weeks
Information^a^	✓				
Information and consent^b^		✓			
Confirmation of eligibility		✓			
Clinical/physical examination, rheumatoid arthritis		✓	✓	✓	
Routine blood analysis		✓	✓	✓	
Questionnaire EQ5D		✓	✓	✓	
Questionnaire HAQ		✓	✓	✓	
Biomarkers^c^		✓			
Patient booklet^d^		✓	✓	✓	✓
Administration/dispensation of biotherapy^e^		✓			
Biobank^f^		✓		✓	
Concomitant treatments		Collection throughout the study			
Adverse effects collection		Collection throughout the study			

^a^ Inclusion: The inclusion visit should be done in 2–3 weeks

^b^ Information and informed consent: The patient will sign informed consent for the main study and additional consent (optional) if they accept 6-month and 1-year inclusion samples, which will be retained for the creation of biobank

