### Data management {19}

Electronics case report forms (eCRFs) will be used that comply with the general and specific good practice standards, as well as the highest requirements for computer validation, with restricted access at the user level, provided with inconsistency detection filters and with traceability of all the information until the final closing of the study. CRFs must be completed for each subject screened/enrolled in this study. This also applies to patients who do not complete the full follow-up planned in the trial.

All CRFs must be filled out by the personnel duly authorized to do so, who will have access codes to the application for entering personal and non-transferable data. The investigator will keep the records and data during the trial in compliance with all legal and regulatory provisions in force. All data must be supported by original documents in the test center. Any record or document used as a source of information (which will be called the “original data of the subject”) will be kept for review by authorized representatives of the promoter or regulatory bodies. The CRFs will be filled in as soon as possible after the evaluation has been carried out.

All the dates that appear in the CRFs referring to analytical tests and other data must coincide with the dates in which the samples were obtained or the procedures were performed.

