### Adverse event reporting and harms {22}

In each study visit, the presence of the most common adverse events related to the study medication will be actively inquired by the blind investigator, including
-Infections including pulmonary and urinary infections and opportunistic infections including tuberculosis;Nausea, vomiting, abdominal pain, diarrhea, tiredness, dizziness, and headache;Liver problems;Hematological disorders: agranulocytosis, thrombocytopenia, anemia, aplasia;Demyelinating diseases: multiple sclerosis and optic neuropathies;Heart failure;Stevens-Johnson syndromes and Lyell syndromes;Psoriasis;Interstitial pneumonitis;Hypersensitivity reactions: fever, chills, pruritus, urticarial, dyspnea, chest pain, hypotension or arterial hypertension, and reactions to injection sites

Regarding the notification of severe adverse events, we will follow the definitions and guidelines of the document MEDDEV 2.7/3 review 05/03/2015 “Guidelines on medical devices: Clinical investigations: Serious adverse event reporting under Directives 90/385/EEC and 93/42/EEC”.

All adverse events will be followed until its resolution, subject’s death, or lost to follow-up.

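### Patients who stop because of an adverse event are withdrawn without follow-up under one rule and followed to resolution under another, and events that begin after withdrawal are not actively sought

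*Protocol article*

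**What the plan says.** The protocol article deals with this in several places.

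- **Criteria for discontinuing or modifying allocated interventions {11b}** lists the grounds for stopping. One is "occurrence of adverse events, including malignancy"; others include lack of response at the 3-month visit, loss to follow-up and withdrawal of consent. The section closes with the consequence: "Patients discontinuing the intervention will not be followed up and will be withdrawn from the study". No safety exception is attached.
- **Adverse event reporting and harms {22}** sets out how events are found: "In each study visit, the presence of the most common adverse events related to the study medication will be actively inquired". It then sets how long they are pursued: "All adverse events will be followed until its resolution", the patient's death, or loss to follow-up. It also refers notification of severe events to a European medical-device guideline.
- **Plans to promote participant retention and complete follow-up {18b}** says that participants will be "educated in the significance of research follow-up even if they decide to discontinue the study drugs", and collects phone and email contacts.
- **Participant timeline {13}, Table 1** enters adverse effects as "Collection throughout the study".
- **Data management {19}** requires a case report form for every patient and adds: "This also applies to patients who do not complete the full follow-up planned in the trial".
- **Section {20c}** on non-adherence and missing data provides: "For each patient that leaves the study before its completion, the cause will be collected".

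**The concern.** This point is about safety follow-up, not about the missing 6-month response. There are two problems.

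1. **Events already open at withdrawal.** A patient who stops because of an unresolved event falls under both {11b} and {22}, and they direct opposite actions. One site may close the record at exit while another follows the event to its end, and each could cite the protocol.
2. **Events that begin after withdrawal.** Section {22} does not reach these in practice. It pursues events once they are known, but it looks for them at study visits, and {11b} ends those visits.

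At stake are consistent observation of patients who stopped a biologic because it harmed them, and the completeness of the safety record in a trial that has safety in its title. The article describes no between-arm safety analysis, so no bias in such an analysis is claimed.

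**Working it through.** The plan gives no figure on this point, so there is none to reproduce. The check is a comparison of rules followed by a count from the visit schedule.

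**Step 1: do the two rules apply to the same patient?** Section {11b} makes an adverse event a reason to stop, and stopping leads to withdrawal without follow-up. Section {22} covers all adverse events. A patient who stops because of an unresolved event is therefore under both.

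**Step 2: does section {22} contain an end point that reconciles them?** Its end points are resolution, death and loss to follow-up. Discontinuation and withdrawal are not among them. Loss to follow-up cannot stand in for withdrawal required by the protocol, because {11b} and {20c} each list it as a reason separate from adverse events.

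**Step 3: does another section rank the rules?**

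| Section | What it settles | Observation after exit? |
|---|---|---|
| {18b} | Tells patients that follow-up matters after stopping drug | Points to continued follow-up, but sets no rule and does not mention {11b} |
| {19} | Forms are completed for non-completers too | No |
| {20c} | Records why the patient left | No |
| {23} | Monitors data completeness and safety | No |
| {22}, guideline reference | Notification of severe events | Not stated to extend past exit |

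None ranks them.

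**Step 4: are new events sought after withdrawal?** Active inquiry takes place at study visits ({22}). Collection runs for the duration of the study (Table 1). Under {11b} a withdrawn patient has no further visits and is no longer in the study. No section provides another route. No section says outright that new events go unsought; it follows from these three stated rules together.

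**Step 5: how much observation is lost per patient if {11b} is applied as written?**

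Inputs: clinical follow-up of 6 months (Trial design {8}); post-baseline clinical visits at M3 and M6 (Table 1), so 2 inquiry visits.

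Visits lost = scheduled visits after the stop ÷ 2. Months lost = (6 − month of stopping) ÷ 6.

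- Stop before M3: M3 and M6 are lost, 2 of 2 visits. The stop is earlier than month 3, so more than 6 − 3 = 3 of 6 months are lost.
- Stop at M3: M6 is lost, 1 of 2 visits, and 6 − 3 = 3 of 6 months.

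Table 1 lists only the patient booklet at M12, so M12 is not counted above. Counting it would give 3 of 3 and 2 of 3 visits.

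**The case against.** The strongest reply is that the rules can be reconciled. Section {22} is the specific rule on harms, names its own end points and covers every adverse event, while {11b} is a general rule on participation. Letting the specific rule govern open events gives effect to both, and {18b} and {19} lean the same way. That reading is reasonable, but the document does not adopt it and the wording of {11b} is categorical. If granted, it settles only events already open.

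A second reply is that a safety window after withdrawal is the kind of detail a journal article leaves to the full protocol. That would hold if the article were silent. Here it prints a rule ending follow-up and ties inquiry to visits, so the gap comes from what is stated.

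A third is that the cited device guideline may cover the matter. It is not shown. The article uses it for notification of severe events and does not say that it restores follow-up after exit.

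Finally, the consequence is limited. The drugs have a known safety profile ({5d}), patients return to standard care ({30}), and most probably stay with their usual rheumatologist ({14}). No estimate, test or sample size changes. This stands, and it limits the severity. Clinical care does not ensure that the trial records what happens, however, and the trial has no independent safety oversight committee ({5d}).

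**Conclusion.** The concern holds and should be fixed. The conflict between {11b} and {22} for open events is explicit and unresolved. The absence of active inquiry for later events is an inference, but it follows directly from the stated rules and applies to every ground for stopping, including non-response at M3.

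The per-patient losses in the working assume that {11b} is applied literally and that M3 and M6 are the inquiry visits. The number of patients affected is unknown because no discontinuation rate is given. The point does not threaten the primary result.

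**What to change.** Replace the closing rule of {11b} with text to this effect: stopping the allocated biotherapy ends treatment, not study follow-up; unless consent is withdrawn, open adverse events are followed as section {22} describes, and new adverse events are sought through M6 by phone or from the routine clinic record. Record the outcome of each event and the date of last safety contact in the eCRF. Because {11b} also lists pregnancy as a ground for stopping, the same sentence could, as an optional addition, provide for following an exposed pregnancy to its outcome.

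The cost is one wording change, two or three eCRF fields, and a few calls or record checks using the contacts already collected under {18b}. No extra visits are needed. The Trial status section reports recruitment as still under way, so on this document an amendment could still take effect.
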